## Abstract

**Background:**

Caesarean section is a commonly performed operation worldwide. It has been found to increase rates of maternal infectious morbidities more than five times when compared to vaginal delivery. Provision of intravenous prophylactic antibiotics 30 to 60 minutes prior to caesarean section has been found to reduce post-caesarean infection tremendously. Many centers recommend provision of a single dose of antibiotics, as repeated doses offer no benefit over a single dose.

At Bugando Medical Centre post caesarean infection is among the top five causes of admission at the post-natal ward. Unfortunately, there is no consistent protocol for the administration of antibiotic prophylaxis to patients who are designated for caesarean section. Common practice and generally the clinician’s preference are to provide repeated dosages of antibiotic prophylaxis after caesarean section to most of the patients. This study aims to determine the comparative efficacy of a single dose of gentamicin in combination with metronidazole versus multiple doses for prevention of post caesarean infection.

**Methods/Design:**

The study is an interventional, open-label, two-armed, randomized, single-center study conducted at Bugando Medical Centre Mwanza, Tanzania. It is an ongoing trial for the period of seven months; 490 eligible candidates will be enrolled in the study. Study subjects will be randomly allocated into two study arms; “A” and “B”. Candidates in “A” will receive a single dose of gentamicin in combination with metronidazole 30 to 60 minutes prior to the operation and candidates in “B” will receive the same drugs prior to the operation and continue with gentamicin and metronidazole for 24 hours. The two groups will be followed up for a period of one month and assessed for signs and symptoms of surgical site infection.

Data will be extracted from a case record form and entered into Epi data3.1 software before being transferred to SPSS version 17.0 for analysis. The absolute difference in proportion of women who develop surgical site infection in the two study arms will be the effectiveness of one regime over the other.

**Trial registration:**

Current Controlled TrialsISRCTN44462542.

## Background

Postpartum infection remains among the top five causes of pregnancy-related maternal mortality and morbidity worldwide [1-3]. Women who undergo caesarean section have a 5- to 20-fold greater risk of postpartum infection than women having a vaginal delivery [4-7]. The incidence of post-cesarean infection varies widely worldwide from 2.5% to 20.5% [8-12].

Post-caesarean infections are polymicrobial, involving aerobes, anaerobes and ureaplasma. The main source of postpartum infection after caesarean section is the lower genital tract, particularly if the membranes are ruptured, but this still occurs with intact membranes following preterm birth. The most common isolated pathogens are anaerobes and gram-negative aerobes. Gram-negative aerobes include *Escherichia coli, Klebsiella* spp, *Enterobacter* spp. and *Proteus* spp*.* The anaerobes include *Bacteroides* spp*., Clostridium* spp.*,* and *Fusobacterium* spp*.*[8-10]*.* However, exogenous bacterial contamination by skin flora (such as *Staphylococcus aureus*) as a result of a break in sterile technique, may occur, especially following a difficult or complicated surgery [11]. Mawalla *et al.*, in a prospective cross-sectional study, reported that most common isolates in surgical site infection at Bugando Medical Centre are gram-negative bacteria. *Staphylococcus aureus* was found in only 28.6% of study patients; and 18.8% were MRSA (Methicillin resistant *Staphylococcus aureus*) [12].

Selection of antibiotics for prophylaxis follows the principle that the selected antibiotic regimen should have activity against the microbial agent commonly involved in surgical site contamination and actual infection. A combination of clindamycin and aminoglycosides has been recommended as the treatment of choice in post-caesarean infection, since it covers most of the pathogenic bacteria commonly involved. Alternatively, a combination of metronidazole with aminoglycosides has been found to be effective in some studies [8,10,13,14]. Apart from being a drug of choice in treating gram-negative bacteria, methicillin sensitive *Staphylococcus aureus* responds to gentamicin [14-16].

A number of well-designed studies have documented the efficacy of prophylactic antibiotics in reducing the rates of post-partum infection among patients who have undergone caesarian section [17-21]. Administration of antibiotic prophylaxis within an hour prior to skin incision is more effective in reducing post-caesarean infectious morbidity when compared to administration of the same drugs after cord clamping, and has no effect on neonatal infection [22-26]. Owens *et al.*, in a systematic review, reported that provision of antibiotic prophylaxis for caesarean section before skin incision compared with after umbilical cord clamping is associated with a 40% decrease in postpartum endometritis and a 30% decrease in wound infection [27].

Provision of a single dose of antibiotics preoperatively has been found to be as effective as multiple doses, in prevention of postpartum infection [28,29].

At Bugando Medical Centre (BMC), the rate of caesarian is estimated to be 20% [30]. All patients who deliver by caesarian section receive antibiotic prophylaxis. There is no consistent protocol for administration of antibiotic prophylaxis for patients designated for caesarean section The common practice is to provide repeated doses of prophylactic antibiotics for at least 24 hours after caesarian section and often on individual clinicians’ practice and preference. Gentamicin and metronidazole are among the antibiotics which are used as prophylaxis for infection during caesarean delivery.

This study aims to compare the efficacy of an intravenous single dose of gentamicin (3 mg/Kg) plus metronidazole 500 mg given 30 to 60 minutes before incision and multiple doses of gentamicin (3 mg/Kg) plus metronidazole (500 mg) 30 to 60 minutes before incision and every 8 hours for 24 hours postoperatively.

### Justification for this study

Caesarean section remains an important risk factor for post-partum infection in many health facilities. Surgical site infection post-caesarean section is among the top five causes of admission in the postnatal ward at Bugando Medical Centre. There is no consistent protocol for provision of prophylactic antibiotics at our obstetric unit. Therefore, the findings from this study will help to improve the quality of care by using standard protocol for antibiotic prophylaxis among patients undergoing caesarean section.

### Study hypothesis

In this study, the hypothesis is: “there is no clinically significant difference between a single dose of gentamicin in combination with metronidazole and multiple doses over 24 hours for prevention of post caesarean infection".

## Methods/Design

### Study design and site

This is an interventional, open label, two-armed, randomized, single center study to be conducted at BMC, a zonal consultant and teaching hospital situated in Mwanza City, Tanzania. In this hospital, 7,149 pregnant women are admitted yearly. There are 6,868 deliveries per annum, 1,398 (20.3%) pregnant women deliver by caesarean section [30].

### Targeted population

The targeted study population is all pregnant women who are admitted at the BMC labor ward and planned for emergency caesarean section.

### Sample size estimation

The incidence of surgical site infection ranges between 2.5% and 20%. Zelenitsky *et al.*, in his prospective randomized study, found that deep surgical site infection rates were 8.1% and 6.9% in the single high dose and multiple standard dose groups, respectively [31].

For the purpose of this study, which involves candidates who undergo emergency or non-elective caesarean section, we use Ps = 8.1%, which is the proportion of participants in the single dose antibiotic prophylaxis group expected to develop surgical site infection post caesarian section, and Pn = 6.9%, which is proportion of participants in the multiple dose antibiotic prophylaxis expected to develop surgical site infection. If we assume the hypothesized difference, D to be 5%, the sample size needed to reject this hypothesis at alpha = 0.05 and beta = 0.20 is [32]:

(1)$${\left({\text{Z}}_{0.95}\;\text{+}\;{\text{Z}}_{0.80}\right)}^{2}\;\left[\text{Ps}\left(1-\text{Ps}\right)\text{Pn}\;+\left(1-\text{Pn}\right)\right]/{\left(\text{Ps-Pn-D}\right)}^{2}$$

Substituting to the formula, the total required sample size: 444 (that is, the required sample size in each group will be 222).

When considering 10% of participants drop out or are lost to follow-up, the required sample size will be 490; that is, each group will contain 245 participants.

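### The stated 222 per group does not follow from the protocol's own inputs, which need 594 per group; power to exclude a 5-point excess is about 45%, not 80%

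*Protocol article*

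**What the plan says.** All the inputs are in the section on sample size estimation.

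- Single-dose arm: "we use Ps = 8.1%, which is the proportion of participants in the single dose antibiotic prophylaxis group expected to develop surgical site infection".
- Multiple-dose arm: "Pn = 6.9%, which is proportion of participants in the multiple dose antibiotic prophylaxis expected to develop surgical site infection".
- Difference and error rates: "D to be 5%, the sample size needed to reject this hypothesis at alpha = 0.05 and beta = 0.20".

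The formula uses Z at 0.95 and Z at 0.80, so the test is one-sided, and its denominator is (Ps − Pn − D)². The result is given as: "Substituting to the formula, the total required sample size: 444 (that is, the required sample size in each group will be 222". A 10% allowance for drop-out raises this to 245 per group, and the abstract carries the total forward: "490 eligible candidates will be enrolled in the study".

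**The concern.** The outcome is adverse, and the arm being tested for adequacy (single dose) is assigned the higher rate. The assumed 1.2-point disadvantage therefore uses up part of the 5-point allowance and leaves 3.8 points to work with. A distance that short, at event rates near 7% to 8%, needs far more than 222 women per group.

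The figure sets the size of the whole trial. If it is wrong, the claimed beta of 0.20 is wrong too, and the trial would be more likely than not to miss its target under its own assumptions. The study hypothesis is one of no clinically relevant difference, and the results are meant to shape the hospital's prophylaxis protocol. An imprecise null result could then be taken as support for the single dose.

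**Working it through.** **Inputs** (all from the sample size section): Ps = 0.081, Pn = 0.069, D = 0.05, Z(0.95) = 1.645, Z(0.80) = 0.842.

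**Formula**, with the variance bracket in its usual form:

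n per group = (Z0.95 + Z0.80)² × [Ps(1 − Ps) + Pn(1 − Pn)] / (Ps − Pn − D)²

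- (Z0.95 + Z0.80)² = 6.183 (unrounded z)
- Variance sum: 0.081 × 0.919 + 0.069 × 0.931 = 0.13868

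**Trying to reproduce 222**

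| Denominator | z values | n per group |
|---|---|---|
| (0.081 − 0.069 − 0.05)² = 0.038² = 0.001444, as printed | unrounded | 593.8 |
| same | 1.64 + 0.84 | 590.7 |
| (0.081 − 0.069 + 0.05)² = 0.062² = 0.003844 | unrounded | 223.0 |
| same | 1.64 + 0.84 | 221.9 |

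The stated 222 appears only with 0.062². Two slips would produce it: adding D instead of subtracting it, or swapping the two rates on substitution, since (0.069 − 0.081 − 0.05)² is also 0.062². Either one treats the single dose as 1.2 points better.

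**Other readings tried** (per group)

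- Two-sided alpha with the printed denominator: about 754.
- Variance as above, true difference set to zero: 343 one-sided, 435 two-sided.
- Equivalence by two one-sided tests with equal rates: 441 to 510.
- Superiority, 8.1% against 6.9%: 5,957 or more.
- Superiority on a 5-point difference: 208 to 634, depending on the base rate, sidedness and continuity correction. None of these equals 222.

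**Requirement**

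- Before drop-out: 594 per group, 1,188 in total.
- With 10% drop-out: 594 / 0.9 = 660 per group, 1,320 in total. The protocol's own step from 222 to 245 looks like multiplication by 1.1 (222 × 1.1 = 244.2); done that way, 594 becomes 654 per group.

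**Power of the planned size**, as Φ(0.038/SE − z) with SE = √(0.13868/n)

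- n = 222: SE = 0.02499, and 0.038/0.02499 = 1.520. One-sided 5%: Φ(1.520 − 1.645) = 0.45. Limit of a two-sided 95% interval: Φ(1.520 − 1.960) = 0.33.
- An exact binomial check of the same Wald rule at n = 222 gives 0.46 and 0.34.
- n = 245 with no drop-out: 0.48 and 0.36.
- n = 222 with the difference reversed: Φ(0.062/0.02499 − 1.645) = 0.80. This is the power the protocol claims.

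**Sensitivity**

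- Equal true rates at n = 222, one-sided 5%: 67% power at 6.9%, 64% at 7.5%, 61% at 8.1%. For 80% power, 318 per group are needed at 6.9% and 369 at 8.1%.
- Margin for which 222 per group does give 80% power at 8.1% against 6.9%: 0.012 + 2.487 × 0.02499 = 0.074, or 7.4 points.

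**Typographical note.** The printed bracket has a displaced plus sign, Ps(1 − Ps)Pn + (1 − Pn). Read literally it equals 0.9361 and gives about 4,008 per group. It was evidently not used, and it does not explain 222.

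**The case against.** - **The cause is inferred.** The article shows no working, and with unrounded z the reversed difference gives 223.0, not 222. This stands as a caution about how the slip arose. It does not touch the mismatch, because the printed denominator gives 594 whatever the mechanism.
- **The 45% belongs to a test the analysis section does not spell out.** D is called a hypothesized difference and never a non-inferiority margin. The data analysis section plans a test for a significant difference with 95% confidence intervals. This is fair: the 45% must be read as power to exclude a 5-point excess at one-sided 5%, with rates of 8.1% and 6.9%. That is, however, the only test the sample size formula can refer to, and the one to which the stated beta of 0.20 applies.
- **The background section regards a single dose as equally effective, so equal rates might be the fairer scenario.** The sample size section nevertheless states unequal rates, and equal rates still leave power at 61% to 67%.
- **Some alternative calculations land near 444**, such as 435 or 441. Those are per-group numbers, whereas the protocol says 444 is the total.
- **The formula bracket is a typesetting slip.** Agreed. Repairing it leads to 594, not 222.

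**Conclusion.** The concern holds. With the protocol's own rates, difference, alpha and denominator, the requirement is 594 per group (1,188 in total), about 2.7 times the stated 222 (444). At 222 evaluable per group, power to exclude a 5-point excess is 45% one-sided at 5%, or 33% against the limit of a two-sided 95% interval, where 80% is claimed. Nothing elsewhere in the article supports 444.

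The result rests on three things: the normal approximation with unpooled variance (the exact check agrees within about a point), reading D as the excess to be ruled out, and the stated rates of 8.1% and 6.9%. That the 1.2-point difference was entered in the wrong direction is an inference, though the only reading tried that reproduces the stated figure.

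**What to change.** In the sample size section:

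1. Correct the bracket to Ps(1 − Ps) + Pn(1 − Pn), and evaluate the denominator as (0.012 − 0.05)².
2. Replace 444 and 222 by 1,188 and 594 as the number required for 80% power.
3. Then take one of two routes:
   - Enrol to that requirement, about 1,320 with 10% drop-out, and change the enrolment figures in the abstract and the envelope counts in the randomization section to match. This is a large step: the site reports 1,398 caesareans a year, and recruitment was due to end on 15 May 2012.
   - Keep 490 as the feasible number, and say openly that it falls short of the requirement. State that 222 evaluable per group give about 45% power for a 5-point difference at 8.1% against 6.9% (one-sided 5%), and about 64% if both rates are 7.5%.

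The second route costs a protocol correction and a less favourable power statement, with no extra participants. If it is taken, it would help to add that an interval which fails to exclude a 5-point excess will be reported as inconclusive and not as equivalence. The arithmetic correction does not depend on that sentence.

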### Quality control

The principal investigator will review data daily from case record forms (CRF) for completeness and consistence of the responses.

Two data clerks, ensuring that entered data quality will not rely on a single person, will conduct data entry. Where discrepancies are found, the two data entry clerks will be called together with the CRF to rectify the difference.

Participation refusal or the decline from study of a significant number of eligible women (more than 30%) may create uncertainty in the internal validity of the study.

Efforts will be made to explain to all eligible women the nature of the study and its importance for improving the care of women delivering by caesarean section at Bugando. We anticipate an attrition rate of 10% or less. Study participants will be reminded to attend their follow-up days through contact phone numbers provided by them.

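### The 490 women enrolled do not leave the stated 444 after a 10% loss: 441 remain, a minor shortfall of 3

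*Protocol article*

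**What the plan says.** The section on sample size estimation assumes infection risks of 8.1% (single dose) and 6.9% (multiple doses), a hypothesised difference D of 5%, alpha 0.05 and beta 0.20. After its formula it gives "the total required sample size: 444", which it splits into 222 per group. It then allows for loss: "When considering 10% of participants drop out or are lost to follow-up, the required sample size will be 490", and adds that "each group will contain 245 participants". The step from 222 to 245 is not shown.

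The quality control section returns to the loss rate: "We anticipate an attrition rate of 10% or less". The randomization section prepares about 490 envelopes, 245 of them for arm A and the rest for arm B, so the same enrolment figure is used there.

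**The concern.** The 10% is described as a share of participants, that is, of the women enrolled. An allowance of that kind should leave the required number after the loss has been taken off. Here the required number, the loss rate and the enrolled number are printed next to each other and do not agree. The likely cause is that 10% of the smaller number (those needed) was added, although the loss is taken from the larger number (those enrolled).

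What is at stake is the correctness of a stated design figure. The same step, applied to any corrected base, would again leave 1.1 x 0.9 = 0.99 of the requirement, 1% short apart from rounding.

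**Working it through.** **Inputs** (all from the sample size section): 444 required, 222 per group; loss 10%; 490 enrolled, 245 per group; Ps = 0.081; Pn = 0.069; D = 0.05; beta 0.20; alpha 0.05, one-sided because the formula uses Z at 0.95.

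**1. Reproducing 490.** Adding 10% to each group gives 222 x 1.1 = 244.2, rounded up to 245, and 2 x 245 = 490. This is an exact match. Working on the total gives 444 x 1.1 = 488.4, which rounds up to 489, so rounding per group is the better explanation. The multiplication is inferred from this match.

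**2. What 490 leaves.** 490 x (1 - 0.10) = 441, or 220.5 per group on average. The shortfall is 444 - 441 = 3 women, and 3 / 444 = 0.7%. This step needs only the printed figures and not the inference in step 1.

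**3. What a 10% loss needs.** n / (1 - 0.10) = 222 / 0.9 = 246.7, rounded up to 247 per group, or 494. That is 4 more than 490, and 4 / 494 = 0.8%.

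**4. The loss that 490 does cover.** (490 - 444) / 490 = 46 / 490 = 9.4%.

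**5. Effect on power.** The variance term is taken in its usual form, Ps(1 - Ps) + Pn(1 - Pn) = 0.074439 + 0.064239 = 0.138678. Power is Phi(distance / sqrt(0.138678 / n) - 1.645), with n per group.

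| Distance | n = 222 | n = 220.5 | Change |
|---|---|---|---|
| 0.038, the size of the printed Ps - Pn - D = 0.081 - 0.069 - 0.05 | 45.0% | 44.8% | about 0.2 points |
| 0.062, the value that reproduces 222 (Ps - Pn + D) | 79.8% | 79.6% | about 0.2 points |

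**6. Status of the base.** With exact normal quantiles, (Z0.95 + Z0.80)^2 x 0.138678 / 0.038^2 = 593.8, or 594 per group. The figure 222 appears only with 0.062 in the denominator: 2.48^2 x 0.138678 / 0.062^2 = 221.9, using the rounded quantiles 1.64 + 0.84. With exact quantiles it is 223.0. The sign of D therefore appears to have been reversed when the numbers were put in. The bracket as printed is not the usual variance; taken literally it gives about 4,008 per group.

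**7. Carry-over to a corrected base.** With 594 per group, the 1.1 step gives 653.4, rounded up to 654 (1,308 in total). After a 10% loss 1,177 remain, about 11 short of 1,188. Dividing by 0.9 gives 660 per group, or 1,320.

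**The case against.** The strongest reply is that this is too small to matter. Three women in 444 is 0.7%, no conclusion of the trial would turn on it, and 10% is a planning ceiling. The quality control section expects that rate or less, so the plan falls short only if loss lands between 9.4% and 10%. All of that stands, and it is why the point is minor. It does not remove the point, because an allowance stated at 10% should hold at 10%.

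A second reply is that no inflation formula is printed, so the method is not known. That is also true, and the 1.1 step is an inference. The mismatch between 490, 10% and 444 does not depend on it.

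A third reply is that a condensed article may leave detail to the full protocol. That does not help here, because nothing is missing: the figures that disagree are all printed.

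Three stronger readings are tempting and are not supported:

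- A reader might infer that the loss allowance leaves the trial materially underpowered. It costs about 0.2 points. The low power at the printed distance comes from the base calculation.
- A reader might infer that enrolment should rise to 494. That figure is right only for a base of 444, which the printed distance does not give.
- A reader might take 79.8% as the plan's own power. It rests on a distance of 0.062, which appears nowhere in the document; the printed expression gives 0.038.

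**Conclusion.** The point holds as a small arithmetic error. Enrolling 490 does not leave 444 after the stated 10% loss; it leaves 441, and it protects 444 only up to a 9.4% loss. The size is 3 evaluable women (4 in enrolment) and about 0.2 percentage points of power, whichever distance is used.

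This assumes that the 10% is a share of women enrolled, which is the natural reading of the sentence, and that women lost contribute no primary outcome. The power figures also assume the usual unpooled variance and a one-sided 5% test. The larger question, that 222 does not follow from the printed distance, is separate, and changing the loss allowance would not settle it.

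**What to change.** Restate the sentence in the sample size section in one of two ways: 490 enrolled leaves 441 evaluable at 10% loss, or 490 keeps 444 evaluable up to a loss of 9.4%. Either is a change of wording. Neither needs more women or a different number of envelopes.

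When the base sample size is itself corrected, apply the allowance as n / (1 - 0.10) per group, round up, and print the formula. Do not adopt 494 in the meantime. The extra cost of the right step is small: on a base of 594 per group it is 1,320 against 1,308, or 12 women.

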### Eligibility/Enrollment

After the decision for caesarean section is made, the pregnant woman will be assessed to see if she is eligible for this study. The assessment for eligibility will be based on inclusion and exclusion criteria given below.

